## Abstract

**Introduction:**

Knee osteoarthritis (OA) is a chronic secondary musculoskeletal pain condition resulting in disability, reduced quality of life, and high societal costs. Pain associated with knee OA is linked to increased sensitivity in sensory, cognitive, and emotional areas of the brain. Self-regulation training targeting brain functioning related to pain experience could reduce pain and its associated disability. Self-regulatory treatments such as mindfulness meditation (MM) and electroencephalography neurofeedback (EEG-NF) training improve clinical outcomes in people with knee OA. A feasibility clinical trial can address factors that could inform the design of the full trial investigating the effectiveness of self-regulation training programmes in people with knee OA. This clinical trial will evaluate the feasibility, safety, acceptability, experience and perceptions of the self-regulatory training programmes.

**Methods:**

The proposed feasibility trial is based on a double-blind (outcome assessor and investigators), three-arm (MM usual care, EEG-NF + usual care and usual care control group) randomised controlled parallel clinical trial. Participants with knee OA will be recruited from the community and healthcare practices. A research assistant (RA) will administer both interventions (20-min sessions, four sessions each week, and 12 sessions over three successive weeks). Feasibility measures (participant recruitment rate, adherence to interventions, retention rate), safety, and acceptability of interventions will be recorded. An RA blinded to the group allocation will record secondary outcomes at baseline, immediately post-intervention (4th week), and 3 months post-intervention. The quantitative outcome measures will be descriptively summarised. The qualitative interviews will evaluate the participants' experiences and perceptions regarding various aspects of the trial, which includes identifying the barriers and facilitators in participating in the trial, evaluating their opinions on the research procedures, such as their preferences for the study site, and determining the level of acceptability of the interventions as potential clinical treatments for managing knee OA. Māori participant perceptions of how assessment and training practices could be acceptable to a Māori worldview will be explored. The interviews will be audio-recorded and analysed thematically.

**Discussion:**

This trial will provide evidence on the feasibility, safety, and acceptability of the MM and EEG-NF training in people with knee OA, thus informing the design of a full randomised clinical control trial.

## Introduction

Knee osteoarthritis (OA) is a chronic secondary musculoskeletal pain condition resulting in disability, reduced quality of life, and high societal costs (1, 2). Knee OA was among the top-ranked conditions in terms of the number of years lived with disability (3). Chronic pain in knee OA is often attributed to structural changes in joint structures. However, there is an apparent discordance between the nature and intensity of the pain and the degree of structural changes in the knee joints (4, 5). Pain associated with knee OA is linked to increased sensitivity in sensory, cognitive, and emotional cortices of the brain and psychological contributions (6–17). Self-regulation training targeting normalising brain functioning related to pain experience could improve clinical outcomes (18–24).

Mindfulness meditation training (MMT), a form of self-regulation training, ‘*involves focussed attention to the changing sensations of the body (usually the breath) and non-reactive monitoring of arising sensory events*’ (19). Several mechanisms that mediate pain relief following MMT have been identified (25). Neuroimaging studies confirm that MMT can modulate activity in the cortical areas processing sensory, cognitive, and emotional components of the pain experience. MMT improves mood, increases autonomic modulation, and engages non-opioid mechanisms that could mediate pain outcomes (26–38).

Electroencephalography neurofeedback (EEG-NF) is a biofeedback training designed to improve health outcomes. The EEG-NF training involves assisting people to learn to self-regulate the activity of specific brain areas that are involved in key functions related to pain perception and disease. In the EEG-NF training, a real-time feedback (reward) is provided when the participant's brain activity reaches the set threshold frequency level of the targeted cortical electrical activity (39–48). Evidence demonstrates a clinically significant reduction in pain following the EEG-NF training (49–55). NF also improves anxiety, emotional regulation, brain activity, and autonomic modulation, potentially mediating mechanisms of pain reduction (56–63). Pilot EEG-NF training targeting infraslow frequency bands demonstrated encouraging patterns for pain outcomes in people with chronic musculoskeletal pain (64, 65).

Both MMT and NF are stand-alone, promising self-regulatory interventions demonstrated to improve pain outcomes. However, evidence of the effectiveness of these two self-regulation training methods is lacking in people with knee OA, a common chronic secondary musculoskeletal pain condition. Although both interventions appear to rely on self-regulatory principles, the physiological and psychological mechanisms through which these two interventions improve pain outcomes may be different (63–69). Therefore, identifying the mechanisms for how these self-regulatory interventions improve outcomes can assist in further optimising protocols to enhance outcomes. Thus, the primary aim of the full clinical trial will be to assess the clinical effectiveness and cost-effectiveness of MMT + usual care and EEG-NF training + usual care against usual care for improving pain and functional outcomes in individuals with knee OA. The secondary aim of the full randomised clinical trial will be to identify the psychological and physiological mechanisms by which training reduces pain and improves function.

However, prior to conducting this full RCT, we propose conducting a feasibility trial to address the factors that could influence the design of the full clinical trial (64). The feasibility issues/questions that require understanding prior to conducting a full-powered RCT are as follows: Are mindfulness meditation and neurofeedback training feasible, safe, and acceptable interventions for people with knee OA? What are the participant recruitment, enrolment, adherence, and dropout rates? What are the adverse side effects of these two self-regulation-based training programmes? What are the participant's experiences of the treatment and research procedures, particularly Māori perceptions of how assessment and training practices in the trial are acceptable to cultural perspectives and values, including Te Ao Māori (a Māori worldview)? What modifications are required for the full trial? What sample size is required to conduct an adequately powered trial?

Therefore, the objectives of this feasibility randomised clinical trial are as follows:
•Objective 1: To determine the feasibility (i.e., rates of participant recruitment, enrolment, training compliance, retention/dropouts) of conducting the full randomised clinical trial.•Objective 2: To examine the safety of the administered interventions.•Objective 3: To explore the participants' perceptions regarding the study procedures, including the acceptability of interventions.•Objective 4: To explore Māori perceptions of how assessment and training practices in the trial are acceptable to cultural perspectives and values, including Te Ao Māori (a Māori worldview).•Objective 5: To derive the central tendency and variability of the clinical outcome measures to inform the sample size of a full clinical trial.

## Research design and methods

This protocol was reported in accordance with the CONSORT statement on pilot/feasibility studies (69). This trial is prospectively registered in the Australian New Zealand Clinical Trials Registry (ANZCTR 12621001741875). The trial has been documented following the recommendations outlined in the Interventional Trials (SPIRIT) statement and the template for intervention description and replication (TIDieR) checklist (Table 1) (70).

**Table 1 T1:** Description of the EEG-NF and MMT, based on the template for intervention description and replication.

Item number and item	Description
1. **Brief name** Provide the name or a phrase that describes the intervention.	Mindfulness meditation training (MMT) Electroencephalography neurofeedback (EEG-NF) training
2. **Why** Describe any rationale, theory, or goal of the elements essential to the intervention.	Infraslow frequency (<0.1 Hz) is a brain electrical rhythm with maximal spectral power in frequencies below 0.1 Hz. The phase of ISF is correlated with amplitudes of higher frequency bands. Altering ISF may normalise electrical activities across resting-state brain networks that are altered in people with chronic pain (17). The region of interest for EEG-NF training is the pregenual anterior cingulate cortex (pgACC). pgACC is a cortical area processing emotional information and is functionally connected to brainstem centres responsible for endogenous inhibitory function. The EEG-NF training programme is designed to up-train the ISF at the pregenual anterior cingulate cortex (pgACC) to promote greater modulation of sensory inputs. A brief MMT regimen involves participants focussing on the sensation of each breath occurring at the tip of the nose. MMT regimen will influence psychological processes, including anxiety, cognition and attention and promote pain relief via non-opioid mechanisms.
3. **What** Materials: Describe any physical or informational materials used in the intervention, including those provided to participants or used in intervention delivery or training of intervention providers. Provide information on where the materials can be accessed (e.g., online appendix, URL).	Each participant will wear an EEG cap with sensors fixed to the scalp and connected to a 21-channel DC-coupled amplifier (BrainMaster Technologies, Inc.). ISF sLORETA software (Neurofeedback Services of New York) will be used for ISF-NF training.
4. **Procedures:** Describe each of the procedures, activities, and/or processes used in the intervention, including any enabling or support activities.	Participants will be seated. Participants will be instructed to close their eyes, relax, and listen to the sound feedback. The participants will be instructed to minimise eye blinks, eye/head/neck movements, swallowing manoeuvres, and teeth clenching. The software programme will play a distinct tone when the brain activity of participants reaches the set threshold of infraslow magnitude at the pgACC. The RA-1 will be trained remotely by the Centre for Mindfulness (UCSD) to provide an MMT regimen in the trial. MMT involves instructing participants to focus on the sensation of each breath occurring at the tip of the nose. As a progression, the participants will be instructed to broaden their focus to the ‘full flow of the breath’, including bodily sensations. The participants will be instructed to acknowledge thoughts, feelings, and emotions as they arise without judgment and ‘simply return their attention back to the breath sensations’.
5. **Who provided** For each category of intervention provider (e.g., psychologist, nursing assistant), describe their expertise, background, and any specific training given.	A research assistant trained in delivering both interventions will administer the training.
6. **How** Describe the modes of delivery (e.g., face-to-face or by some other mechanism, such as internet or telephone) of the intervention and whether it was provided individually or in a group.	All participants will receive individual face-to-face training sessions.
7. **Where** Describe the type(s) of location(s) where the intervention occurred, including any necessary infrastructure or relevant features.	Interventions will be delivered in the School of Physiotherapy laboratory, University of Otago, Dunedin, New Zealand.
8. **When and how much** Describe the number of times the intervention was delivered and over what period of time, including the number of sessions, their schedule, and their duration, intensity, or dose.	The participants will undergo training for 12 sessions, four times a week, for three consecutive weeks. Each training session will last for a 30 min duration.
9. **Tailoring** If the intervention was planned to be personalised, titrated or adapted, then describe what, why, when, and how.	The BrainMaster training programme will provide feedback (reward) according to the real-time brain states of the study participants.
10. **Modifications** If the intervention was modified during the course of the study, describe the changes (what, why, when, and how).	Not applicable. This is a protocol for a feasibility trial.
11. **How well** Planned: If intervention adherence or fidelity was assessed, describe how and by whom, and if any strategies were used to maintain or improve fidelity, describe them.	A research assistant providing training will record the number of training sessions attended by participants (i.e., adherence rates). Adherence rates will be summarised at the end of training. An investigator will monitor the fidelity of the intervention.
12. **Actual:** If intervention adherence or fidelity was assessed, describe the extent to which the intervention was delivered as planned.	Not applicable. This is a protocol for a feasibility trial.

### Study design

This feasibility study (71, 72) will be a double-blind (outcome assessor and all investigators), three-arm randomised control parallel trial with participants having an equal probability of being assigned to each arm. The study outcome measures will be collected at baseline, immediately post-intervention (4th week), and 3 months post-intervention.

### Ethical approval

Ethical approval was obtained from the NZ Health & Disability Ethics Committee. The Ngāi Tahu Research Consultation was obtained. The School of Physiotherapy health and safety committee will act as an internal Data and Safety Monitoring Board.

### Establishing whakawhanaungatanga (relationships) with Māori

Osteoarthritis is an increasing health condition among the Māori population. Improving the OA treatment will help in reducing health inequalities between Māori and non-Māori (17, 73–80). Combining our consultation with the Ngāi Tahu Research Committee, Māori researchers, and research work conducted by Māori on chronic pain, we will implement practices acceptable to a Māori worldview, thus being responsive towards the cultural and health needs of the Māori people. The clinical trial will be guided by a Māori-centred research approach (i.e., Kaupapa Māori research) that incorporates cultural considerations and provides an interpretive framework aligned to Māori customs (tīkanga) base. A Māori researcher (SA) with expertise in issues about kaumātua living with OA will oversee the implementation of tīkanga principles and administer culturally appropriate strategies to recruit Māori participants. We will adhere to Māori rituals of engagement, such as pōwhiri and hui, on Marae and wharenui (meeting house in Marae). This will involve presenting the background and procedures of the study, as well as the findings from previous work on lived experiences of pain among Māori. In addition, we will discuss culturally appropriate pain assessment tools for Māori with OA, as well as involve their family and whānau in the community. Hui will be carried out face-to-face (kanohi-ki-te-kanohi) to enable the community to see who the researchers are and include whanaungatanga (strengthening connections). Engaging participants with respectful behaviour closely related to Māori customs, such as ‘aroha’ and ‘manākitanga’. The priority will be getting the community talking about interventions for reducing pain, improving function, and strengthening referral networks of Māori living with OA into the research. A Māori researcher will conduct interviews with Māori participants. In hui and interviews, as well as assessment and intervention sessions, the importance of whānau support means that Māori participants can bring families and friends for the assessment and treatment sessions. Furthermore, koha (such as food, drink, and a voucher) will be offered as a mark of appreciation at each interview. In prioritising mana (respect) for the participants, Māori culture considers the head sacred (‘he tapu te upoko’). Therefore, permission must be obtained at every EEG-NF session before touching the participant's head. Finally, the research outcomes will be fed back to the community to offer nurturing guidance (awhi) and community relationship building. In this way, the research process and outcomes form lasting relationships beneficial to both the research and the community.

## Study eligibility criteria

The inclusion criteria of the study are as follows: Adults (45–85 years) will be eligible to participate if they meet the clinical criteria for the diagnosis of knee OA according to the guidelines established by the American College of Rheumatology (ACR) and with knee pain that persisted for longer than 3 months, (81). The exclusion criteria of the study are as follows: Recent soft tissue injuries of the knee (e.g., ligaments, muscles, meniscus, tendon) in the last 3 months, infective/inflammatory arthritis, scheduled for joint replacement surgery within the next 4 months, joint injections (hyaluronic acid) in the last 6 months, joint injections (steroids) in the last 3 months, brain injury or diseases (e.g., stroke, multiple sclerosis, Parkinson's disease), spinal cord injury or diseases, nerve injuries or neuropathy in the legs, migraine or recurrent headaches, cognitive illness (dementia)—any difficulty thinking, reasoning, or remembering, major psychiatric illnesses and former neurosurgical procedures of the brain, and recent/current pregnancy.

## Study location and settings

### Recruitment strategy

We will recruit participants from the wider Dunedin community. Community newspapers [The Star (a free newspaper published weekly) and the Otago Daily Times (a paid newspaper published daily)] will periodically publish study advertisements, reaching out to the urban area of Dunedin city, its suburbs, and other nearby villages. Sponsored Facebook adverts will also be implemented. Targeted advertisements will be published in community organisations, including arthritis advocacy groups and community-based exercise classes. Patients attending primary healthcare practices based in Dunedin will also be invited to participate.

The participants in the experimental groups will get a reimbursement of $200 in the form of supermarket/travel vouchers as a compensation for their time dedicated to this study. It is anticipated that each participant will contribute approximately 20 h to the study, including three 2-h assessments [baseline, post-intervention (4th week), and 3 months post-intervention], 12 1-h training sessions, and 1 h of a qualitative interview.

The participants in the usual care group will get a reimbursement of $80 in the form of supermarket/travel vouchers as a compensation for their time dedicated to this study. It is anticipated that each participant will contribute approximately 8 h to the study, which includes three 2-h assessments and 1 h of a qualitative interview.

### Māori sampling

The purposeful sampling strategy will be conducted with people identifying as being of Māori ancestry and ethnicity that meet our sampling criteria. Key informants will initially be identified through the Māori researcher and research teams' whānaungatanga (networks and relationships) and Māori healthcare providers (73). The snowball sampling method will involve asking the initial respondents to suggest others, precisely who they know in the target group and whom to contact and invite to take part in the research. A Māori-specific participant information sheet will clearly outline the purpose of the study and emphasise that the information provided by Māori participants, their family, and their whānau could contribute to the acceptability of the study as a potential clinical treatment for the management of knee OA from a Māori perspective. A Māori investigator will train the research staff on Tikanga Māori to create a safe and respectful atmosphere for all participants during the trial.

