### Allocation

After the baseline assessment, the participants will be allocated into one of the three study groups with equal probabilities. Blocks of unequal length, with the measurements and the possibilities of these lengths unknown to other investigators, will be used to promote allocation concealment. The senior biostatistician, using non-informative group allocation codes, will generate the allocation sequence using a standard computer software.

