### Blinding

The outcome assessor and all investigators will be blind to the group allocation. The participants and the intervention provider will not be blinded to the intervention because the content will be evident. The biostatistician will be blinded to the study groups until all planned analyses are completed, thus minimising bias during data analysis. All the participants will be requested to keep their treatment allocation group private from the outcome assessor during the duration of the study. This information is detailed and indicated to the participants within the study information sheet.

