**Figure 1 F1:**
[figure not shown]
A model wearing an EEG Combi Cap.

We will use the EEG- NF programme administered in our pilot studies in people with chronic musculoskeletal pain, including knee OA (64, 65). Infraslow frequency (<0.1 Hz) is a brain electrical rhythm with maximal spectral power in frequencies below 0.1 Hz. Influencing the ISF may normalise electrical activities across resting-state brain networks that are altered in people with chronic pain (87–90). The pgACC is the chosen region of interest (ROI) for the training due to its connectivity with the periaqueductal grey matter (PAG), which promotes endogenous pain inhibition (17, 90, 91). Up-training ISF at the pgACC improved the pain outcomes in people with chronic pain (65). Therefore, the EEG-NF training programme was designed to up-train the ISF at the pgACC to improve pain outcomes through promoting greater sensory modulation, altering attention and cognitive controllability of pain.

The participants in the control group who are receiving usual care will continue to receive treatments as usual. However, they will refrain from practising meditation during the study period. Following the trial completion, they will be offered to receive one of the trainings.

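### Linked Māori participants are randomised individually and may bring companions, but exposure to mindfulness in the EEG-NF arm goes unrecorded and companions are not asked to protect assessor blinding

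*Protocol article*

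**What the plan says.** All references are to the protocol article.

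- **Recruitment (Māori sampling).** The first contacts come from existing networks: "Key informants will initially be identified through the Māori researcher and research teams' whānaungatanga (networks and relationships) and Māori healthcare providers". Recruitment then widens by referral: "The snowball sampling method will involve asking the initial respondents to suggest others, precisely who they know in the target group".
- **Companions (Establishing whakawhanaungatanga with Māori).** "Māori participants can bring families and friends for the assessment and treatment sessions".
- **Randomisation (Allocation).** After baseline, "the participants will be allocated into one of the three study groups with equal probabilities". No household, whānau or referral unit is named.
- **Privacy (Blinding).** "All the participants will be requested to keep their treatment allocation group private from the outcome assessor during the duration of the study". The section adds that this is set out in the information sheet.
- **Usual care (end of EEG-NF training, after Figure 1).** Participants in this arm continue usual treatment, but "they will refrain from practising meditation during the study period". No matching instruction is stated for the EEG-NF arm.
- **Delivery (Table 1, item 6).** "All participants will receive individual face-to-face training sessions". The MMT section describes spoken guidance on attending to the breath and mentions no equipment.
- **Measurement (Table 2).** The five-facet mindfulness questionnaire is collected at baseline and both follow-ups. No item asks about meditation outside the allocated arm or contact with another participant's training. The section on the outcome assessor says that the effectiveness of blinding will be measured.

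**The concern.** Each of these choices is reasonable alone. Together they enrol people who know one another, assign them to different arms one at a time, and let companions into the room where a simple verbal technique is taught. A companion, or the participant at home, could pass the technique to someone in another arm.

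The arms are not equally open to this. Usual care carries an instruction not to meditate; EEG-NF has none stated. Mindfulness in the EEG-NF arm would blur the comparison of the two trainings. The Introduction says that their mechanisms may differ, and the Discussion sets separate brain-activity hypotheses for them. It would also mix a mindfulness component into the EEG-NF versus usual care contrast. The Quantitative data analyses plan says that these between-group models will be run in this trial.

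A second route concerns blinding. Companions may attend assessment sessions run by the blinded research assistant, but the stated request for discretion binds participants only.

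The Introduction also asks what modifications the full trial will need. Whether recruitment through networks spreads an intervention between arms is one such question. Exposure that is not recorded during follow-up is hard to recover afterwards.

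**Working it through.** **Inputs from the article.** 20 participants per arm, three arms, 3 × 20 = 60, which agrees with the stated total. For scale, the minimal clinically important difference given for the full trial is 1.8 points on the pain scale.

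**Inputs not in the article.** The number of linked pairs and the share of exposed people who take up meditation. I assume 2, 4 or 6 separate pairs to show a range.

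**Chance that a linked pair is split,** treating 20:20:20 as a simple random split and ignoring blocking:

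- different arms: 40/59 = 68%
- exactly one in mindfulness: 2 × 20 × 40/(60 × 59) = 1600/3540 = 45%
- one in mindfulness, one in EEG-NF: 2 × 20 × 20/(60 × 59) = 800/3540 = 22.6%, about 23%
- one in mindfulness, one in usual care: the same 23%, but here the no-meditation instruction applies

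With each person allocated independently, the first three become 2/3, 4/9 and 2/9, so the result hardly depends on the approximation.

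**Expected mindfulness/EEG-NF pairs and an upper bound on their effect.** Each such pair holds one EEG-NF participant who could be exposed. Suppose that every one of them takes up mindfulness and gains a full 1.8 points on top of EEG-NF. The EEG-NF mean then moves by 1.8 × (expected pairs)/20.

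| Linked pairs (assumed) | Expected MM/EEG-NF pairs | Share of EEG-NF arm | Shift in arm mean, points |
|---|---|---|---|
| 2 | 2 × 0.226 = 0.45 | 2.3% | 0.04 |
| 4 | 4 × 0.226 = 0.90 | 4.5% | 0.08 |
| 6 | 6 × 0.226 = 1.36 | 6.8% | 0.12 |

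Even on this assumption the shift is small against 1.8 points.

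**Scale for the full trial.** If a share c of a comparison arm took up the whole mindfulness effect, the difference would shrink to 1.8(1 − c), and the sample needed would grow by 1/(1 − c)². For c = 5% this gives 1.71 points and a factor of 1.11; for c = 10%, 1.62 points and 1.23. The article gives no value for c, and as planned the trial would not supply one.

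**The case against.** The case for leaving the plan alone has real force.

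- **Usual care has a safeguard.** A reader might infer that mindfulness can pass freely to both other arms and quote the 45%. The article does not support that. Usual-care participants are told not to meditate, which addresses the practice that would cause contamination even though it does not stop sharing. The route without a stated safeguard is EEG-NF, at half that figure.
- **Permission for companions is not permission to cross over.** A reader might infer that someone enrolled in another arm may sit in on mindfulness sessions. The article offers whānau support; it neither allows nor excludes this case. Training is individual and runs over 12 sessions led by a trained assistant, so hearing about it at home is not the same exposure.
- **This is a condensed article.** The information sheets, including the Māori-specific one, are not shown, so it cannot be concluded that nobody is asked to keep the technique to themselves. What can be said is that the request the article does describe is directed at participants and at the assessor.
- **Indirect checks exist.** The mindfulness questionnaire could show an unexpected rise in another arm, interviews cover all arms, and blinding is to be assessed. None of these identifies linked participants or asks about exposure.
- **Numbers may be small.** The Discussion itself warns of inadequate Māori representation.

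These points limit the concern to EEG-NF, to companions at assessments and to the secondary contrasts. They do not remove the case for recording exposure while it can still be recorded.

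**Conclusion.** The point stands as a cheap improvement, not as an error that undermines the trial. The stated arrangements leave one route for mindfulness without a stated safeguard, into the EEG-NF arm, and one gap in assessor blinding, through companions. About 23% of linked pairs would be split between mindfulness and EEG-NF. With 2 to 6 assumed pairs that is roughly 0.5 to 1.4 pairs, and fewer actual exposures if not every pair shares the technique.

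A reader might go further and infer that the feasibility results or the planned sample size are compromised. They are not, to any material degree. Recruitment, adherence, retention and safety rates hardly depend on cross-exposure. The full-trial sample size is to be built from standard deviations, repeated-measure correlations and a fixed 1.8-point difference, not from the contrast observed here. What is at stake is the interpretation of the exploratory between-group estimates and what the full trial can learn about recruiting through networks.

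The verdict rests on some linked participants being enrolled, which snowballing makes likely, and on the breath-focus technique being teachable by word of mouth, which its description suggests.

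**What to change.** Keep snowball recruitment and whānau support, and add three things:

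1. At enrolment, record whether the person lives with, or was referred by, another participant.
2. Extend the request in the Blinding section to accompanying whānau and friends. Ask participants and companions not to share training content with other participants until the 3-month assessments are done.
3. At the post-intervention and 3-month assessments, ask every arm about meditation practice and about exposure to another participant's training. This also checks the existing usual-care instruction.

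Whether an enrolled whānau member may sit in on another arm's sessions should be left to the investigators and the Māori researcher. It trades a small dilution of exploratory contrasts against support that the Kaupapa Māori approach treats as integral. The wording of item 2 should be agreed with the Māori researcher for the same reason.

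The cost is a few lines in the information sheets, one enrolment field and one or two questionnaire items, added to an assessment load that the Discussion already acknowledges as a burden.
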